#### Blood samples and parameters

Blood samples are collected at each visit and immediately used for peripheral blood mononuclear cell (PBMC) isolation (T0), analysis by the study laboratory and centrifugation to freeze plasma samples at −80°C (T0–T11). A clinical standard laboratory report is generated after every visit for each study participant (table 2). In addition to routine blood parameters, anticitrullinated protein antibody, zonulin, fatty acid binding protein 2 and calprotectin levels are measured. Aliquots are securely stored to account for novel observations and testing of hypotheses.

**Table 2 T2:** Routine blood parameters measured at each timepoint (T0 for cross-sectional study, T0–T11 for longitudinal study)

Haematology—EDTA-blood	Clinical chemistry—serum
Basophils, %	Albumin
Basophils, abs.	Alanine Transaminase (ALT), 37°C
Eosinophils, %	Alkaline phosphatase, 37°C
Eosinophils, abs.	Aspartate Transferase (AST), 37°C
Erythrocytes	Bilirubin, total
Haematocrit	Cholinesterase
Haemoglobin	Cholesterol
HbA1c	Creatinine
Leucocytes	high-sensitivity C-reactive protein (hs-CRP)
Lymphocytes, %	Glucose, serum
Lymphocytes, abs.	Gamma-GT, 37°C
Mean corpuscular hemoglobin (MCH)	High density lipoprotein (HDL)-cholesterol
Mean corpuscular hemoglobin concentration (MCHC)	Low density lipoprotein (LDL)-cholesterol
Mean corpuscular volume (MCV)	Potassium
Monocytes, %	Sodium
Monocytes, abs.	Total protein
Neutrophils, %	Triglycerides
Neutrophils, abs.	Uric acid
Platelets	Urea/Blood Urea Nitrogen
Red cell distribution width (RDW)	Proteins—serum
Reticulocytes	Rheumatoid factor H 35.9
Reticulocytes	Hormones—serum
Reticulocytes, abs.	Insulin
	Thyroid stimulating hormone (basal)

#### Stool, urine and saliva samples

The samples listed in box 1 are collected at each visit, except for stool samples on T2 (fasting week) and immediately frozen and stored at −80°C. Stool characteristics are recorded at the time of the sampling. Faecal samples represent the main sample type for resolving the dynamic processes driven by microbiome in the gut. Also, as the gut microbiome is prone to diurnal fluctuations, the stool samples are collected in the morning, as far as possible.

### Methods applied to samples

#### Biomolecular extractions

The collected stool samples undergo a biomolecular extraction procedure to allow isolation of concomitant DNA, RNA, proteins, peptides and metabolites from single, unique faecal water samples; this process involves cryomilling the samples in liquid nitrogen, disassociating metabolites from membrane and cell wall components in a solvent mixture of methanol, chloroform and water and lastly proteins and RNA extraction by a methanol/chloroform and phenol buffer.^53 54^ Faecal water is recovered following centrifugation and filtration, at low speed or low flow, respectively, to avoid cell lysis. Nucleic acids are preserved by the addition of ribonuclease inhibitors and isolated by silica column-based techniques. This protocol involves the use of a robotic platform, ensuring a higher level of standardisation and reproducibility.^2^

#### Coupled MG and MT analyses

Prior to sequencing library preparation, internal standards are introduced to obtain quantitative sequencing data.^55^ Contamination-free MG and MT data are generated, processed and analysed using the integrated meta-omics pipeline (IMP),^45^ which incorporates preprocessing, assembly, gene annotation, mapping of reads, single nucleotide polymorphism calling, data normalisation as well as analyses of community structure and function in a fully reproducible software framework based on Docker. The MG and MT data are specifically screened for enrichments in genes and pathways with known immunogenic properties.^56^ The extracellular biomolecules are linked to specific microbial populations based on the intracellular MG data.^57^ In addition, the sequencing data are mapped against genomes of food components.^44^ The quantitative data are also related to microbial population sizes to determine the contribution of the resolved microbial populations in stool to the extracellular DNA and RNA complements.^58^

#### Metaproteomics

For the metaproteomic analyses, filtration is used to separate extracellular peptides from the obtained (poly)peptides. The resulting smaller fractions are then desalted and analysed without proteolytic digestion via liquid chromatography (LC) and mass spectrometry (MS) on an EasyNano-LC coupled online to a QExactive-Plus mass spectrometer (ThermoScientific, Waltham). The identification of ribosomal peptides is done with an integrated catalogue of MG and MT data, while the non-ribosomal peptides are identified using different tools, that is, MyriMatch, DirecTag as well as CycloBranch.^45 59 60^ The metaproteomic data also allow identification of extracellular (poly)peptides with possible pathogenic functions including protein misfolding and molecular mimicry.^61 62^

#### Metabolomics

Metabolomic data are analysed using a combination of targeted and untargeted approaches.^44 54 63^ This highlights the major metabolite classes produced by the gut microbiome with an effect on human physiology, including organic acids, SCFA, lipids, branched-chain fatty acids, branched-chain amino acids, vitamins, bile acids and neurotransmitters. Besides external compound calibration series for quantification and quality control samples to ensure data normalisation and data acquisition quality assessment, the metabolite extraction fluid is fortified with multiple internal standards to improve method precision and accuracy.^64 65^ The data are compared with in-house databases and public mass spectral libraries to identify known metabolites. The metabolomic data complement the MG and MT data and, thus, allow further establishments of conclusive links to metabolic properties in the gut.

#### Deep immune profiling

Deep immune profiling is done using a recently established and optimised panel of metal-labelled antibodies together with cytometry coupled to MS, the Maxpar Direct Immune Profiling System (MDIPA). This approach allows the simultaneous quantification of 38 parameters on single cells. Whole blood is stained with the MDIPA kit and stabilised with Proteomic stabiliser Prot-1 (501351694, Smart Tube, Las Vegas) before storage at −80°C. The quantified immune cells included in the MDIPA panel are CD3+, CD4+, CD8+, monocytes, dendritic cells, granulocytes, mucosal-associated invariant T cells (MAIT), T cells, natural killer (NK) and B cells.^66^ Cytokine expression profiles are analysed on blood plasma using the Human Luminex performance Cytokine Panel (R&D Systems Europe, Abingdon), measuring CCL3, CCL4, CCL5, GM-CSF, IL-1b, IL-2, IL-4, IL-5, IL-6, IL-8, IL-10, IL-12p70, IL-13, IL-15, IL-18, IL-21, IL-27, IL-33, IFN-b, Galectin-1, IFN-g and TNF-a.^56^

#### Gut-on-a-chip models

PBMCs isolated from T0 blood samples are co-cultured with gut-derived microbes under physiologically representative conditions using the gut-on-a-chip model HuMiX.^67^ This model of the human gastrointestinal interface allows the investigation of the interactions between immune, epithelial and bacterial cells and specifically the response to fasting in personalised in vitro models.

#### The expobiome MAP

The Expobiome Map (https://expobiome.lcsb.uni.lu) illustrates the diverse complex of microbial immunogenic molecules, including nucleic acids, (poly)peptides, structural molecules, and metabolites. The interactions between this “expobiome” and human immune pathways are encoded in the context of chronic diseases.^1^ The ExpoBiome Map is visualised using the MINERVA Platform.^68^ Clicking on different elements on the map reveals factors they affect and are affected by, allowing an easier navigation through the complex relationships between individual microbiome components in relation to human disease. The multi-omics data generated in the present study will be integrated with the Map.

#### Exploratory analysis of novel host-microbiome interactions

Unknown non-ribosomal peptides or metabolite features are associated through correlation with transcripts, proteins, and metabolites. Extracellular DNA fragments, as well as transcripts, proteins and ribosomal peptides are linked to their genomic context by using IMP.^45^ The data generated by the project will be connected and collated to existing, publicly available datasets.

### Outcome parameters

#### Primary outcome

The primary endpoint of the study is the characterisation of the gut microbiome. The evaluation includes both between-group and within-group differences in the longitudinal study arms with the fasting intervention.

#### Secondary outcome measures

Secondary outcomes include the identification of common and disease-specific molecular signatures and the characterisation of microbiome-derived effector molecules impacting the innate and adaptive immune pathways. Furthermore, several additional parameters mentioned in *Anthropometric data and questionnaires* are assessed over a period of 12 months.

### Sample size and power calculation

A power calculation using pilot MT data based on faecal extracellular RNA samples was performed to determine the number of subjects to be recruited for the ExpoBiome project. The obtained relative abundances of genera were used for the calculation of the required sample size per group. The power calculation was based on the algorithm as described by Tusher, Tibshirani, and Chu.^69^ To achieve a power of 90% (at α=0.05), a total of 50 individuals per group (RA, PD, healthy controls) must be analysed. Considering any possible dropouts, 20% additional subjects are recruited, resulting in a total number of 180 individuals, that is, 60 per group. For the longitudinal part, a subset of 60 adult individuals (30 patients with PD and 30 patients with RA) are selected, based on their ability and willingness to participate in the longitudinal part of the study (12 months follow-up). The selected number of participants for the longitudinal study is based on feasibility due to the complexity and high costs of the clinical trial. The total number of subjects in the longitudinal study can be smaller, as each individual serves as their own control.

### Adverse events

There are no major risks expected for participants. Minor common adverse effects of PF might include headaches, nausea, insomnia, back pain, dyspepsia and fatigue.^70^ Any occurring adverse events are recorded at each visit in REDCap.^52^ Serious adverse events are communicated to the study coordinator and principal investigator within 24 hours of their report.

### Data management, monitoring, analysis and evaluation of data

The study participants receive a study ID (pseudonym), which is used for all collected data. Self-administered questionnaires are directly recorded in REDCap. Participant files are kept for at least 10 years at the respective clinical sites.

Weekly meetings between the study team, the different clinical partners and the principal investigator ensure a close monitoring of the data. Any occurring adverse events or other issues are, thus handled immediately.

Different statistical tests are performed according to the nature of the data. A premature termination of the study is not envisaged; therefore, no interim analysis is done. Different correlation measures are applied, including Spearman correlation, mutual information on discretised data, distance correlation, maximum information criterion, local similarity analysis and the bioenv approach. Comparison across all omic levels allows identification of common and disease-specific signatures. Multivariate machine learning is used to link different data features to observed patterns. For additional confounding factors, especially in the cross-sectional study, multivariate statistical analysis will be performed. These factors will be accounted by including confounders in the analysis, for example, as covariate in the statistical models.

The longitudinal part of the study continues for a period of 12 months. After finalisation of this period, there is no follow-up of the participants. Interesting findings will be further validated using the existing sample set and analyses may be performed on additionally collected samples.

The Standard Protocol Items: Recommendations for Interventional Trials checklist was used to write this protocol.^71^

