## Methods and analysis

### Study objectives

The first objective of the study is to define specific gut microbiome-derived molecules in RA and PD, compared with healthy individuals, and relate this information to the immunophenotypes of the individuals. The second objective is to identify and track common and disease-specific molecular signatures to predict the outcome of a gut microbiome-targeted therapeutic intervention, here fasting, on inflammation-driven symptoms in RA and PD. The third objective of the study is to identify and validate microbiome-derived effector molecules, which downregulate pro-inflammatory innate and adaptive immune pathways.

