### Study design

The ExpoBiome cohort consists of 180 adult individuals, meeting the exclusion and inclusion criteria (table 1), for the cross-sectional study (objectives 1 and 3) and 60 adult individuals for the longitudinal study (objectives 2 and 3). There are five different arms in total: (1) RA—cross-sectional arm (60 patients), (2) PD—cross-sectional arm (60 patients) and (3) healthy controls—cross-sectional arm (60 patients), (4) RA—longitudinal arm (30 patients), (5) PD—longitudinal arm (30 patients) (figure 1).

**Table 1 T1:** Inclusion and exclusion criteria

Inclusion criteria	Exclusion criteria
Age 18–79 One of the following diagnoses: rheumatoid arthritis (first diagnosis>6 weeks ago), Parkinson’s disease OR healthy volunteer Control (‘healthy’) individuals must be without any evidence of active known or treated RA, without any evidence of active, known or treated central nervous system disease, and without a known family history of idiopathic PD Control individuals should match the RA or PD individuals as closely as possible (sex, age, education) Present written declaration of consent Ability to understand the patient information and willingness to sign the consent form Consent to specimen collection and specimen use	Gout or proven bacterial arthritis Participation in another study Existing/current eating disorder (bulimia nervosa, anorexia nervosa) within the past 5 years Severe internal disease (eg, kidney deficiency with creatinine >2 mg/dL) Existing vegan diet or fasting during the last 6 months Presence or suspicion of atypical PD (eg, early dementia, early autonomous dysfunction) Diagnosis of chronic inflammatory bowel diseases, coeliac disease or colorectal cancer according to the guidelines of the German Society of Gastroenterology Use of anti-psychotic drugs Antibiotic use during the previous 12 months Start of novel therapy with disease-modifying anti-rheumatic drugs Pregnancy or breastfeeding women Contraindication for additional blood draws (eg, haemoglobin <10) BMI<18.5 Psychiatric illness that limits understanding of the examination protocol (unable to consent)

BMI, body mass index; PD, Parkinson’s disease; RA, rheumatoid arthritis.

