### Recruitment and randomisation

Patients are recruited by the specialised sites via different sources, for example, by direct referral from either a physician at the Immanuel Hospital Berlin and the outpatient department of the Institute of Social Medicine, Epidemiology and Health Economics at Charité-Universitätsmedizin Berlin, or the Paracelsus-Elena Clinic in Kassel, or by non-personal advertising strategies (eg, flyers or social media).

For PD, the patients are screened by an experienced movement disorders specialist for featuring at least two of resting tremor, bradykinesia and rigidity according to the United Kingdom Parkinson’s Disease Society Brain Bank criteria.^48^ Additionally, patients must show evidence of a dopaminergic deficit, either with DaTScan imaging or with a clear response to dopaminergic drugs. Motor and non-motor symptoms are assessed with the MDS-UPDRS (part I–IV), including the Hoehn and Yahr (severity) scale.^49^ Additional PD-specific scales as Parkinson’s Disease Sleep Scale-2, Parkinson’s Disease Questionnaire-39, Non-Motor Symptoms Questionnaire and Non-Motor Symptoms Scale are used.

For patients with RA, the diagnosis has been made prior to the study by an experienced rheumatologist according to the European League Against Rheumatism criteria.^50^ All clinical stages of RA will be included. We excluded patients with a BMI <18.5, as this indicates underweight, and fasting is not recommended. We did, however, not include an upper limit as fasting might be especially beneficial for patients with a BMI >24.9 and more than 60% of patients with RA are classified as overweight or obese.^51^ For comorbidities, we excluded mainly diseases which are known to interfere with the gut microbiome and might be potential confounders.

The chosen exclusion criteria will optimise the pairing process of healthy controls and patients with either RA or PD. However, as we have two diseases with different anthropometric characteristics (including age, gender, BMI) and only one control group, adding additional inclusion and exclusion criteria in the recruitment process would compromise on optimised matching. Furthermore, for the longitudinal part of the study, each patient will serve as his/her own control over time. Participants meeting all the inclusion and no exclusion criteria (table 1) are assigned to their respective groups (RA, PD or healthy control) (figure 1) for the cross-sectional study after written informed consent.

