### Medication

The medical treatments of the patients are monitored and documented with every clinical visit. The fasting intervention might necessitate temporary adjustments of several medications, for example, antidiabetic and antihypertensive drugs as insulin levels and hypertension will be reduced due to lack of food intake.^31^

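### Covariate adjustment for RA and PD drugs in the patient-versus-control contrasts rests entirely on untreated patients, whose number is neither stated nor secured, so drug effects could be reported as disease signatures

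*Protocol article*

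**What the plan says.** The first objective (Study objectives) is to "define specific gut microbiome-derived molecules in RA and PD, compared with healthy individuals". The section on data management, monitoring, analysis and evaluation of data says of the results: "Comparison across all omic levels allows identification of common and disease-specific signatures". The same section foresees multivariate analysis for confounding, especially in the cross-sectional study, and adds: "These factors will be accounted by including confounders in the analysis, for example, as covariate in the statistical models". It names no covariate.

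Table 1 (Study design) requires controls to be "without any evidence of active known or treated RA, without any evidence of active, known or treated central nervous system disease". Matching of controls covers sex, age and education.

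On the patient side, the exclusion that concerns antirheumatic therapy is "Start of novel therapy with disease-modifying anti-rheumatic drugs", so established therapy is eligible. Under Recruitment and randomisation, all stages of RA are accepted, and PD patients must show a dopaminergic deficit "either with DaTScan imaging or with a clear response to dopaminergic drugs". The Medication section says: "The medical treatments of the patients are monitored and documented with every clinical visit". Current medications are also collected at baseline (Anthropometric data and questionnaires).

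**The concern.** Adjusting for a covariate separates two influences only where the covariate varies within both groups, or where one is willing to extrapolate. Under Table 1 no control can be on treatment for RA or PD. A drug given for either disease is therefore zero throughout the control group and, in the patient group, follows the diagnosis closely. Choosing other covariates does not create the missing overlap.

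Objective 1 depends on these contrasts. If a drug alters the microbiome, its effect and the effect of the disease reach the analysis largely as one. A feature that reflects treatment could then be carried forward as specific to RA or PD, into the search for effector molecules (objective 3) and into the Expobiome Map. The own-control argument in the protocol applies to the longitudinal arms and does not protect the comparison with healthy controls.

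**Working it through.** **Inputs**

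- From Sample size and power calculation: 50 analysable per group, power 90%, α = 0.05 (sidedness not stated; two-sided taken here), 20% added for dropout.
- From Table 1: drug indicator = 0 for every control, for drugs given for RA or PD.
- Treated share of patients, p: not in the document. Assumed 50% to 100%.
- Effect of the drug on a feature, g: not in the document. Assumed 0.3 to 0.8 SD.

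**The plan's own figure.** 50 × 1.2 = 60 per group and 3 × 60 = 180 reproduce. The 50 itself does not, because the effect size and variance from the pilot data are not given. As a calibration only, a two-group comparison of means at 50 v 50 has 90% power for (1.960 + 1.282) × √(2/50) = 0.648 SD. That is not the trial's planning effect; it serves below as a yardstick.

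**Drug term fitted.** Take y = a + b × disease + c × drug, with no drug in controls. Then a is the control mean, a + b the mean of untreated patients and a + b + c the mean of treated patients. So b is untreated patients minus controls, and treated patients add nothing to that difference in means.

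- Variance of b: SD² × [1/(n(1 − p)) + 1/n]
- Variance without the drug term: SD² × 2/n
- Ratio: [1/(1 − p) + 1]/2
- Power: Φ(0.648/SE − 1.960), with SD = 1

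| Treated share p | Untreated of 60 | Variance ratio | Power, 60 v 60 |
|---|---|---|---|
| no drug term | – | 1 | 94% |
| 50% | 30 | (2 + 1)/2 = 1.5 | 83% |
| 80% | 12 | (5 + 1)/2 = 3.0 | 54% |
| 90% | 6 | (10 + 1)/2 = 5.5 | 33% |
| 95% | 3 | (20 + 1)/2 = 10.5 | 19% |
| 100% | 0 | not identified | – |

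For example, at 95%: SE = √(1/3 + 1/60) = 0.592; 0.648/0.592 = 1.096; Φ(1.096 − 1.960) = 0.19. With the 50 per group that the plan requires for analysis, power falls from 90% to 75% at p = 50%, 46% at 80% and 28% at 90%. At 100% the disease and drug columns are identical: the design matrix has rank 2 of 3.

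**Is the adjusted estimate biased?** A simulation of 20,000 runs at 50 v 50 used no true disease effect, a drug effect of 0.65 SD, an additive model, and untreated patients who do not otherwise differ. The mean adjusted disease estimate was 0.001 at both 80% and 90% treated, with type I error of 5.2% and 4.9%. Under those assumptions the loss is precision.

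**Drug term left out.** The contrast estimates the disease effect plus p × g. With no true disease effect, SE = √(2/50) = 0.2. At p = 0.8 and g = 0.5 the bias is 0.40 SD, 0.40/0.2 = 2.0, and Φ(2.0 − 1.960) = 0.516. The chance that one feature is nominally significant is:

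| Drug effect g | p = 80% | p = 90% | p = 100% |
|---|---|---|---|
| 0.3 SD | 0.224 | 0.271 | 0.323 |
| 0.5 SD | 0.516 | 0.614 | 0.705 |
| 0.8 SD | 0.893 | 0.950 | 0.979 |

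A multiplicity correction would lower these probabilities but would leave the bias p × g as it is.

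**The case against.** The strongest reply is that the article commits to no particular model. It names no covariate, does not say that antirheumatic or dopaminergic drugs will be entered, and offers covariates as an example. Other protection exists: matching on sex, age and education, and exclusion of recent antibiotics, antipsychotics, newly started antirheumatic therapy and several comorbidities. Covariate lists and within-disease drug analyses are commonly left to an analysis plan, and the medication data for them are collected. All of that is fair. What stands is narrower: none of these measures creates drug overlap between patients and controls, while the article already attaches a disease-specific label to the results.

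Three stronger readings are tempting and go beyond the text.

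- A reader might infer that adjustment can never work. That is strictly true only if every patient is treated. All RA stages and PD patients qualifying by imaging are eligible, so some untreated patients may enrol. The simulation shows that adjustment is then imprecise rather than necessarily biased.
- A reader might infer that controls take none of these agents. Table 1 bars the treated diseases, not the same agents used for another indication.
- A reader might infer that drug effects will be reported as signatures. The document supports only that they could be. Signatures common to RA and PD are also less easily explained by a drug class used in one disease.

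The figures also simplify. Several drug classes and doses are reduced to one yes/no indicator, and the 0.648 SD is a yardstick from a comparison of two means, not the plan's algorithm.

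**Conclusion.** The point holds in a limited form. For drugs given for RA or PD, adjusting the patient-versus-control contrasts rests wholly on untreated patients, and the protocol neither states nor secures their number. If the drug is modelled, the variance of the disease term rises 3.0, 5.5 or 10.5 times at assumed treated shares of 80%, 90% or 95%, and with no untreated patients the effect is not identified. If it is not modelled, the bias is the treated share times the drug effect; 80% treated and 0.5 SD give 0.40 SD.

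The structure follows from the eligibility criteria; the sizes rest on assumed treated shares and drug effects. Lack of bias in the adjusted estimate requires in addition that untreated patients resemble treated ones in stage and duration, which the document gives no ground to assume.

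**What to change.** In the analysis section:

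1. Describe the RA and PD contrasts as treated disease versus healthy control.
2. Use covariates for factors that overlap between the groups: age, sex, BMI and shared co-medication. Include site only if each group is recruited at both sites, which the article does not say.
3. For each feature declared a disease signature, test its association with drug class and dose within RA and within PD, adjusting for disease severity and duration where recorded.
4. Flag features that track the drug as possibly drug-related, not as proven drug effects. Dose may follow severity, so a true disease feature can also track the drug.
5. Report the number of untreated patients in each disease group and show their data as a descriptive sensitivity check.

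This needs no new recruitment or samples, since medication is already documented. The cost is some extra analysis and a more cautious claim for some signatures.
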